***Specific Scenarios***

AF with rapid rate response (average rate > approximately 110 bpmin)

If AF with a rapid ventricular response rate is seen then rate control is relatively urgent, to avoid or reduce the possibility of inappropriate shocks.

Hospital admission may be required to do this, particularly if the patient presents with an inappropriate shock.

Alternatively, an urgent clinical assessment may be appropriate.

Beta blockade will be the treatment of first choice. This could be commenced remotely in the absence of contraindications to B blocker therapy – check for these. Also assess whether there has been any other change in patient management recently and ask for a primary care assessment of electrolytes and renal function.

If already on adequate dose of beta blocker (and not on digoxin), consider digoxin, 500mcg bd for one day, then dose depending on age, weight and renal function. Ask for a primary care assessment of electrolytes and renal function. Verapamil is a third line treatment.

If persistent but not permanent, and if not responsive to rate control, consider cardioversion indication

Consider also

- Has the patient had an exacerbation of heart failure?
- Has the patient got a chest infection?
- Has the patient got thyrotoxicosis? (Particularly if taking Amiodarone)

Amiodarone commencement

Amiodarone may interference with digoxin (digoxin dose may need to be reduced) and i*nterference with warfarin (*Warfarin dose may need to be reduced).

INR clinic appointments may need to be altered/increased in frequency. Also, if the patient has experienced VT then Amiodarone may impact on rate of VT: may be slowed sufficiently so that it fails to meet the detection rate.

It may also impact on defibrillation efficacy due to an increase in defibrillation threshold. This may need formal reassessment - discuss with the responsible physician. Also remember the need for regular surveillance, with six monthly TFTs, LFTs, which should be requested from primary care.

**AFl**

This is a particularly troublesome and not uncommon arrhythmia in CRT patients.

It may not trigger mode switch, and so may persist at relatively high rates, causing worsening heart failure.

Consider:

- Anticoagulation
- Rate control
- Cardioversion
- Cavo-tricuspid isthmus ablation.

In general cavo-tricuspid isthmus ablation will be the treatment of choice for common atrial flutter. For non-isthmus dependent flutter it is likely that ablation will remain the treatment of choice but the needs to be discussed with the responsible physician. Bring all episodes of atrial flutter to the attention of both the physiologist and responsible consultant and initiate a discussion around drug and ablation control.

**5) Ventricular Arrhythmias**

Summary chart:

**
[figure not shown]
**

This chart summarises the approach to ventricular arrhythmias.

Your key role in management of ventricular arrhythmias is to identify their occurrence and change in burden. Both may indicate the need for a change in heart failure therapy, antiarrhythmia drug therapy, device programming (both for detection and therapy) and sometimes a further intervention such as ablation or device revision.

In the main you should discuss all these issues both with the technologist staff and the responsible physician. You should not initiate any therapeutic change without discussion with the responsible cardiologist.

However, you should be sufficiently acquainted with these issues to understand when it is appropriate to initiate a discussion about device therapy.

Do not forget to ensure that there are no changes that have taken place in patient medication or status that may have impacted on susceptibility to arrhythmia. Thus ask for primary care review of renal/electrolyte status and consider other co-morbidities or drug changes. Specifically ask patients questions to evaluate this. We are particularly keen to understand why change is occurring in arrhythmia stability status.

The two main arrhythmias to consider are management of monomorphic and polymorphic ventricular tachycardia as listed above.

Monomorphic ventricular tachycardia, even at fast rates, is often amenable to antitachycardia pacing. The precise programming of this can vary greatly and firm guidelines are difficult due to he breadth of the evidence base and its variability. It is necessary to ensure that all possible is done to avoid delivery of shock therapy when ATP my have been successful and this is the principle that will be adopted by technology staff and physicians. The concept of shock reduction will be specifically addressed during the training period and may be updated over the course of the study.

Antiarrhythmic drugs are useful adjuncts. In patients with a high burden of arrhythmia or with slow VT that is resistant to pace-termination and/or very frequent then catheter ablation may be an excellent therapy.

Polymorphic ventricular tachycardia is likely to be mush less amenable to ablation intervention but care should be taken to evaluate all the other issues mentioned above and in particular change in ischemia status or renal/electrolyte status.

Be aware that arrhythmia burden change will signal deterioration in heart failure status and all the heart failure issues in section 1 must be reviewed.

**Arrhythmia Storm**

When this occurs often the reasons/triggers are unknown. It will result in patient admission to hospital. Retrospective evaluation of data will be appropriate to see if issues were missed but management of the episode itself will be as an in-patient.

**Ventricular Fibrillation**

Patients may experience asymptomatic or nocturnal shock therapies for VF, which has no other impact on their well being. Having ascertained the accuracy of the arrhythmia diagnosis (i.e. appropriate shock therapy by analysis of stored electrograms) and efficacy of therapy no further action is required other than to look for precipitating factors (drug changes/co-morbidity change/renal-electrolyte status). Initiate these assessments in primary care. Also initiate weekly monitoring for 4 weeks to consider potential for underlying heart failure/arrhythmia burden change as a precipitant.

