**6) Device Management**

It is intended that issues to do with device management will be handled by technology staff and the responsible clinicians. However you should familiarize yourself with the troubleshooting issues to allow high-level troubleshooting and to understand when you need to ask for advice.

The headline troubleshooting issues are summarized in the table below and these will be supplemented during the training programme.

| **Problem**  **TO BE IDENTIFIED BY MONITOR** | **Consider**  **DISCUSSION WITH CARDIAC TECH OR CARDIOLOGIST** | **Action**  **WITH CARDIOLOGIST AND CARDIAC TECH** |
| --- | --- | --- |
| **Appropriate shocks** | - Optimise ATP to successfully terminate arrhythmia | - Assess patient for reversible causes e.g. 12 lead ECG and U&E. - Optimise ATP regimes. - Consider anti-arrhythmic drugs - Advise about driving restrictions. - Address quality of life. - Dr assessment |
| **Inappropriate shocks** | - Rate - Rhythm - Discriminators - Noise | - Optimise programming e.g. discriminators, increase detection rate for VF/VT. - Treat misdiagnosed SVT e.g. drugs or ablation. - Check for over-sensing , impedance, lead fracture. - Send for CXR - Dr assessment. - ? turn off therapies |
| **Increased Threshold** | - Lead displacement - Lead fracture - Fluid accumulation | - Increase outputs - Send for CXR - Dr assess CXR - Lead replacement/ reposition. |
| **Increased Impedance**  **Decreased Impedance** | - Lead fracture - Insulation break | - Arm movement checks for inappropriate sensing - Reprogram sensitivity and mode - Check outputs - CXR - Dr assessment - Lead reposition/ replacement |
| **Over/under-sensing** | - Lead issue (fracture/ insulation break/displacement) | - Measure P and R waves - Check lead impedance (see above) - Alter sensitivity – only slightly in V lead - Dr assessment - CXR - DFT - Lead reposition replacement |

*Alerts*

“Alerts” will also be specifically addressed. The monitored device data can be flagged according to importance and will appear on the websites under “Alert” communications. The various manufacturers have, for the moment, to handle the issue of notification and data presentation in different ways. Therefore, during the training programme we will address Alert programming in such a way as to allow monitors to be consistent in their approach to their use whilst allowing flexibility.

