The implanted devices are equipped with “Alert” facilities capable of recognising deterioration in either patient clinical status of change in device system functionality that may threaten system integrity/effectiveness. All Alerts will be programmed on but may be de-featured according to clinical judgement of the consultant cardiologist with clinical responsibility for the patient. This will not be a protocol violation but will be assessed in the study analysis.

In the event of an Alert being triggered then:

For non-automatic transmission the patient will contact the study nurse during office hours and perform a download.

The study nurse will inform the responsible senior clinician of all alert transmissions who will act on alerts and determine appropriate clinical action.

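### The monitoring handbook stops at a search for precipitants after an asymptomatic or nocturnal VF shock, although its own device table lists driving advice and a doctor's assessment for the same event

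*Combined protocol and SAP*

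**What the plan says.** Two places in Appendix II (the Protocol Handbook for Remote Monitoring Staff) apply to the same event.

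- **Section 5, Ventricular Fibrillation.** The case is an asymptomatic or nocturnal shock for VF that has not otherwise affected the patient. The monitor confirms from stored electrograms that the shock was appropriate and that therapy worked. After that, "no further action is required other than to look for precipitating factors". The factors named are drug changes, change in co-morbidity, and renal or electrolyte status. The checks are started in primary care, and weekly monitoring for four weeks is added to look for a further precipitant.
- **Section 6, Device Management table, Appropriate shocks row.** The table runs from a problem identified by the monitor, through "DISCUSSION WITH CARDIAC TECH OR CARDIOLOGIST", to action "WITH CARDIOLOGIST AND CARDIAC TECH". The action column for this row includes "Advise about driving restrictions" and an assessment by a doctor.

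Three other places bear on who gets told. Section 5 opens with "In the main you should discuss all these issues both with the technologist staff and the responsible physician" and adds "You should not initiate any therapeutic change without discussion with the responsible cardiologist". Under Alerts in section 6, "The study nurse will inform the responsible senior clinician of all alert transmissions". Section 4, on atrial flutter, shows how the handbook words a firm escalation rule: "Bring all episodes of atrial flutter to the attention of both the physiologist and responsible consultant".

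**The concern.** A shock confirmed as appropriate under section 5 is an appropriate shock under section 6, so both instructions apply to one patient at one moment. On its face the first ends the matter with a search for precipitants. The second calls for specialist discussion, driving advice and a doctor's assessment. Neither refers to the other or says which prevails.

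The monitor's reading matters because the specialist steps start with the monitor. Section 23 of the protocol has senior clinical staff review troubleshooting data and arrhythmia burden when the monitor asks them to. A monitor who takes the VF paragraph literally has no stated reason to ask. Section 2 of the handbook promises a consistent management change plan across the study, yet two monitors could handle the same shock differently and both be following the handbook. At stake is whether a patient who has had a shock for VF receives the driving advice and medical review that the handbook lists.

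**Working it through.** The check is a comparison of texts. No error rate, power figure or event count is involved.

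**Step 1: is it the same event?** The VF paragraph applies only after electrograms show the shock to be appropriate. The section 6 row is for appropriate shocks and carves out neither VF nor shocks without symptoms. So it is the same event.

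**Step 2: set the row's actions beside the VF paragraph.**

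| Action in the section 6 row | In the VF paragraph? |
| --- | --- |
| Look for reversible causes (ECG, blood tests) | In part: renal and electrolyte status named, 12-lead ECG not |
| Optimise anti-tachycardia pacing | Not named; only the efficacy of therapy is checked |
| Consider anti-arrhythmic drugs | Not named |
| Driving advice | Not named |
| Quality of life | Not named |
| Doctor's assessment | Not named |

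The table shows which steps differ. It does not measure care that patients missed.

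**Step 3: does the added monitoring bring something new?** Section 9 of the protocol sets downloads at one per week. Over four weeks the routine schedule gives 4 × 1 = 4 downloads. Weekly monitoring for four weeks also gives 4 × 1 = 4. The difference is 4 − 4 = 0, so this step adds no scheduled contact that would bring the case to cardiology.

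**Step 4: who receives the case?** Under section 2 of the handbook, primary care tests go through the patient's nominated GP or community heart failure nurse. The VF paragraph therefore does contain a handover to clinicians. It names none to the cardiologist or the technician.

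**Step 5: does other text supply the missing handover?**
- The opening of section 5 sends ventricular arrhythmias to the technologist and physician, but only as the usual course. Its firm rule covers therapeutic changes, and the VF paragraph proposes none.
- The Alerts text has the senior clinician told of every alert transmission. All alerts are programmed on unless the responsible consultant decides otherwise. For devices that do not transmit automatically, the route begins with the patient making contact. The documents do not say whether such a device would warn a patient who had not noticed the shock.
- Section 1 tells the monitor to be ready at every stage to consider discussion with senior staff.

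Each of these makes contact with cardiology likely. None mentions driving, which the documents raise only in the section 6 row.

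**The case against.** The best defence is that the two texts have different jobs. Section 5 tells the monitor what the monitor must do; section 6 describes what clinicians and technical staff do. On that reading the VF paragraph limits the monitor's own work and cancels no clinician's duty. It may also be a deliberate, narrow rule for a confirmed, effective shock that left the patient well, set beside a headline table that training is meant to supplement. The section 5 summary chart, a natural place for an escalation rule, is not shown and cannot be held against the plan. Section 1 says that the handbook does not replace clinical common sense.

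Much of this stands, and it keeps the point minor. It does not remove it. If the paragraph is a deliberate exception, the handbook does not say so and does not say who then gives the driving advice. If it limits only the monitor's own tasks, the section 6 sequence still needs the monitor to pass the case on, and the paragraph names no handover to cardiology.

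Two stronger readings are tempting and are not supported. A reader might infer that the case is passed to no clinician at all; the primary care step shows otherwise. A reader might also infer that patients went without driving advice or review. The documents do not show that. Section 3 of the protocol keeps usual care pathways open to every patient, the discussion and alert rules point towards cardiology, and training may have covered the matter.

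**Conclusion.** The inconsistency is real and minor. Followed literally, the VF paragraph leaves out driving advice and a doctor's assessment, which the handbook lists for the same event, and no other visible text restores the driving advice.

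The conclusion rests on the visible text alone. If the missing chart or the training material sends these shocks to cardiology with driving advice, the practical gap closes and only the wording remains to be tidied. How often the situation arises cannot be given, because the documents contain no rate of asymptomatic VF shocks. The point concerns patient safety and the consistency of the intervention. It has no effect on sample size, alpha or the primary analysis.

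**What to change.** In Appendix II, section 5, Ventricular Fibrillation, replace "no further action is required other than to look for precipitating factors" with: *inform the responsible cardiologist and cardiac technician, who follow the Appropriate shocks row of section 6 (including driving advice and doctor assessment); in addition look for precipitating factors*.

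If the clinical leads intend an exception for these shocks, the paragraph should say so and name who gives the driving advice.

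The cost is one handbook sentence, a notice to the nine sites, and one clinician contact per such shock. The discussion and alert rules may already require that contact. No extra downloads are needed. The SAP describes the interim analysis in the past tense, so follow-up may already be over. In that case the correction serves re-use of the handbook, which matters because section 16 of the protocol envisages wider NHS adoption of the care model.

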**Ventricular Ectopics**

In general these should be ignored unless causing unacceptable symptoms or reducing the efficacy of BiV pacing.

**6) Device Management**

It is intended that issues to do with device management will be handled by technology staff and the responsible clinicians. However you should familiarize yourself with the troubleshooting issues to allow high-level troubleshooting and to understand when you need to ask for advice.

The headline troubleshooting issues are summarized in the table below and these will be supplemented during the training programme.

| **Problem**  **TO BE IDENTIFIED BY MONITOR** | **Consider**  **DISCUSSION WITH CARDIAC TECH OR CARDIOLOGIST** | **Action**  **WITH CARDIOLOGIST AND CARDIAC TECH** |
| --- | --- | --- |
| **Appropriate shocks** | - Optimise ATP to successfully terminate arrhythmia | - Assess patient for reversible causes e.g. 12 lead ECG and U&E. - Optimise ATP regimes. - Consider anti-arrhythmic drugs - Advise about driving restrictions. - Address quality of life. - Dr assessment |
| **Inappropriate shocks** | - Rate - Rhythm - Discriminators - Noise | - Optimise programming e.g. discriminators, increase detection rate for VF/VT. - Treat misdiagnosed SVT e.g. drugs or ablation. - Check for over-sensing , impedance, lead fracture. - Send for CXR - Dr assessment. - ? turn off therapies |
| **Increased Threshold** | - Lead displacement - Lead fracture - Fluid accumulation | - Increase outputs - Send for CXR - Dr assess CXR - Lead replacement/ reposition. |
| **Increased Impedance**  **Decreased Impedance** | - Lead fracture - Insulation break | - Arm movement checks for inappropriate sensing - Reprogram sensitivity and mode - Check outputs - CXR - Dr assessment - Lead reposition/ replacement |
| **Over/under-sensing** | - Lead issue (fracture/ insulation break/displacement) | - Measure P and R waves - Check lead impedance (see above) - Alter sensitivity – only slightly in V lead - Dr assessment - CXR - DFT - Lead reposition replacement |

*Alerts*

“Alerts” will also be specifically addressed. The monitored device data can be flagged according to importance and will appear on the websites under “Alert” communications. The various manufacturers have, for the moment, to handle the issue of notification and data presentation in different ways. Therefore, during the training programme we will address Alert programming in such a way as to allow monitors to be consistent in their approach to their use whilst allowing flexibility.

The implanted devices are equipped with “Alert” facilities capable of recognising deterioration in either patient clinical status of change in device system functionality that may threaten system integrity/effectiveness. All Alerts will be programmed on but may be de-featured according to clinical judgement of the consultant cardiologist with clinical responsibility for the patient. This will not be a protocol violation but will be assessed in the study analysis.

In the event of an Alert being triggered then:

For non-automatic transmission the patient will contact the study nurse during office hours and perform a download.

The study nurse will inform the responsible senior clinician of all alert transmissions who will act on alerts and determine appropriate clinical action.

**7) Ischaemia**

At this stage, the role of devices in evaluating ischaemia burden is unclear. We may choose to adopt clinical practise during the course of the study as information and data become available. This will be discussed during training and updates.

It will be the role of the supervising consultant cardiologist to action review and therapy for ischaemia.

# Abbreviations

A&E Accident and Emergency

ACE Angiotensin-Converting Enzyme

ACM All-Cause Mortality

AE Adverse event

AHA American Heart Association

ARB Angiotensin Receptor Blockers

BHF British Heart Foundation

BMI Body Mass Index

BNF British National Formulary

CEA Cost Effectiveness Analysis

Centre Study centre; synonym for “site”

CRF Case report form

CRT-D Cardiac Resynchronisation Therapy-Defibrillator

CRT-P Cardiac Resynchronisation Therapy-Pacemaker

CV Cardiovascular

DSMB Data and Safety Monitoring Board

eCRF Electronic Case report Form

EQ5D Euroqol 5D

ERC Endpoint Review Committee

HEA Health Economics Analysis

HF Heart failure

HRG Healthcare Resource Group

ICD Implantable cardioverter defibrillator

IEC Independent Ethics Committee

IRB Institutional Review Board

KCCQ Kansas City Cardiomyopathy Questionnaire

LTAD Long Term Assist Device

LVEF Left ventricular ejection fraction

MI Myocardial infarction

MRA Mineralocorticoid Receptor Antagonists

NHS National Health Service

NICE National Institute for Health and Care Excellence

NYHA New York Heart Association

PPA Prescription Pricing Authority

PSSRU Personal Social Services Research Unit

QALY Quality Adjusted Life Year

QoL Quality of life

RCP Remote Care Pathway

REM Remote Event Monitoring

RMS Remote Monitoring Service

SAE Serious Adverse Event

SAP Statistical Analysis Plan

SC Steering Committee

Site Study site; (synonym for “centre”)

SOP Standard Operating Procedure

TSC Trial Steering Committee

UCP Usual Care Pathway

# Section 1. Introduction

## 1.1 Purpose of SAP

This Statistical Analysis Plan (SAP) is based on the final version of the study protocol (Version 19 - 12^th^ March 2014), the study design manuscript^1^ and the charters of the Endpoint Review Committee (ERC) and the Data and Safety Monitoring Board (DSMB) for the REM-HF trial. This SAP aims to further specify the procedures and statistical methods to be applied during the final analysis of the study data.

## 1.2 Trial Overview

### 1.2.1 Title

A randomised controlled trial of REmote Monitoring and evaluation of implantable devices for management of Heart Failure patients (REM-HF).

### 1.2.2 Trial Outline

This is a randomised, multi-centre, open label (non-blinded), parallel group, clinical trial in which patients are randomised to receive either the control/usual care (UCP) or intervention (RCP) pathways on a 1:1 basis. The randomisation is stratified on both Site and Device type (ICD, CRT-D or CRT-P). Recruitment started in September 2011, and the target accrual is 1650 randomised patients (825 per group) but with an event driven design (see 2.3). Follow-up is for a minimum of two years.

